### Recruitment and consent

At least two designated anesthesiologists will participate in the recruitment, randomization, and intervention. One is the attending physician, mainly responsible for the randomization, intervention, and clinical anesthesia in the operating room, and the other is a resident physician, mainly responsible for research recruitment and baseline data collection at the preoperative visit before the patient enters the operating room. The patients will be preliminarily screened by an independent and experienced staff member (Chief Neurosurgery Resident for Consultation) according to the inclusion and exclusion criteria. He will notify the designated anesthesiologists in advance if the patient meets the enrollment criteria, and then the designated resident anesthesiologists will go to the emergency room for preoperative visits, including rechecking the eligibility and obtaining informed consent. Reasons why eligible patients are not recruited for the trial will be documented. The family members will be informed of the relevant information, including detailed investigational treatment and potential risks and benefits, after the patient meets the inclusion/exclusion criteria. In addition, the patients can be formally recruited only after the staff obtains the informed consent of the patients or their next of kin.

### Randomization and blinding

Randomization will occur on the date of craniotomy aneurysm clipping. Permuted block will be used and stratified by the culprit vessel sites, including the middle cerebral artery, anterior cerebral artery, anterior communicating artery, and posterior communicating artery. The ophthalmic artery, internal carotid artery, and posterior circulation arteries will not be included in this study. The randomized digital table was previously computer (STATA 17) generated by dedicated independent staff and loaded into a web-based database. The allocation information will be obtained by the attending anesthesiologist through mobile phone software after the patient enters the operating room. Patients will be randomly allocated to receive either e-SGB or camouflaging in a 1 to 1 ratio. The endpoint assessors, data statisticians, and postoperative treatment team members will be blinded to the treatment group allocation, but the anesthesiologist and neurosurgeons will not be blinded, as they need to participate in the safe administration of related patient care. Patients will be unblinded only if they experience serious adverse events requiring additional visits.

### Intervention

Randomized patients will receive an additional e-SGB or a “camouflage” operation before anesthesia induction and then receive standard care after the operation. In the intervention group, e-SGB will be performed by a designated experienced anesthesiologist using the B-ultrasound visualization technique. The intervention site will be the ipsilateral side of the planned craniotomy site. After routine disinfection, 8–10 mL of 0.5% ropivacaine will be injected into the surface of the longus colli muscle on the medial side of the prevertebral fascia at the level of the C6 anterior tubercle (Fig. 2), and the puncture point will be covered with sterile dressings. The success criterion of e-SGB is Horner's syndrome, which is characterized by miosis, ptosis, enophthalmos, conjunctival hyperemia, and facial redness without sweating. The patient will be monitored for at least 30 min before anesthesia induction to rule out any related complications after SGB. Patients with failed e-SGB will be excluded. In the control group, a blank control was adopted to reduce unnecessary invasive operations. Patients will not undergo any sham procedures and will only be prospectively visited at a specified time point. However, they need to undergo the “camouflage” operation to ensure the smooth implementation of the blinded endpoint evaluation. The anesthesiologist will cover the corresponding part of the patient with sterile dressings to confuse the follow-up, without any puncture. In this way, the follow-up staff would not be aware of the grouping of the participants by the puncture point. All patients will be admitted to the ICU after the operation and then receive the standard of care.

**Fig. 2 Fig2:**
[figure not shown]
Schematic diagram of stellate ganglion block under ultrasound guidance. After routine disinfection, 0.5% ropivacaine 8–10 mL will be injected into the surface of the longus colli muscle on the medial side of the prevertebral fascia at the level of the C6 anterior tubercle, and then the puncture point will be covered with sterile dressings. **B** The ultrasonic image of the cross-section of the sixth cervical segment: the blue arrow indicates the prevertebral fascia; the blue dotted line area is the longus colli muscle, and its lateral highlight area is the distribution of the stellate ganglion; and the green triangle indicates the drug injection site (the inner side of the prevertebral fascia), in which the stellate ganglion can be effectively blocked through the diffusion of the drug solution under the fascia and without nerve injury. C6, the sixth cervical segment; CA, carotid artery; CV, jugular vein; TH, thyroid; at, anterior tubercle; M, muscle; SCM, sternocleidomastoid muscle; LCol, longus colli muscle; LCap, longus capitis muscle; N, nerve from cervical plexus; pt, posterior tubercle. ASM, anterior scalene muscle; MSM, middle scalene muscle

### SGB-related complications

Complications related to SGB can be greatly reduced by ultrasound-guided procedures. Although the incidence is low, experienced anesthesiologists will be involved, and SGB-related complications will be regarded as safety indicators in this study. Patients who present suspicious symptoms within 30 min after e-SGB will be treated immediately, and a preliminary diagnosis will be graded by the anesthesiologist (Table 2). According to the patient’s condition, the anesthesiologist and the neurosurgeon will decide jointly whether to suspend the operation or implement further treatment. For serious complications (grading criteria ≥ 3), additional follow-up may be required to ensure patient safety; in those cases, the patient will be unblinded, but we will continue follow-up outcomes unless the patient or their families request withdrawal from this study. Serious complications, such as subarachnoid block, will be immediately reported to the ethics committee by the PI, and an emergency data monitoring committee meeting will be initiated for consultation. The possible complications of SGB and the time of observation for each are as follows:Block or injury of nerve: recurrent laryngeal, phrenic, brachial plexus, and vagus nerves (30 min after e-SGB and during hospitalization)Injury of the artery: internal carotid and vertebral arteries (30 min after e-SGB)Local anesthetic poisoning (30 min after e-SGB)Subarachnoid block (30 min after e-SGB)Pneumothorax and hemothorax (30 min after e-SGB)Infection and hematoma at the puncture site (during hospitalization)

**Table 2 Tab2:** Classification of complications

Grade	Definition
Grade 1	No need for drugs or surgery, endoscopy, or intervention
Grade 2	Requiring some treatment, including blood transfusions and parenteral nutrition
Grade 3	Requiring surgical, endoscopic, or radiological intervention
3a	Intervention not under general anesthesia
3b	Intervention under general anesthesia
Grade 4	Severe life-threatening complications need to be transferred to the intensive care unit or special care unit
4a	Single-organ dysfunction
4b	Multiorgan dysfunction
Grade 5	Resulting in death

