### Adverse event monitoring report and data monitoring committee

An adverse event (AE) is the development of an undesirable medical condition/complication or the deterioration of a preexisting medical condition following or during exposure to an intervention, whether considered causally related to the intervention. The expected harm/complications will be systematically collected by visiting each patient at each follow-up point, while the unexpected harm/complications will be collected through spontaneous reporting from the patients or physicians in charge. All study-related AEs will be recorded and closely monitored until they are resolved or stable or until it can be confirmed that the study treatment is not the cause of the events. The investigator will immediately report to the research department and advise the PI to determine the severity of the adverse event as soon as it occurs. In addition, it should be reported to the Ethics Committee (IRB) within 24 h, and the PI is responsible for reporting all AEs. The Data Monitoring Committee (DMC) will be responsible for monitoring clinical safety and reviewing all adverse events reported to the IRB to determine the risks and benefits of the study. The DMC is made up of specialists in anesthesiology, neuropathies, ethics, statistics, and methodology. If there were any severe adverse events (SAEs) associated with the study (grading criteria ≥ 3), the DMC was responsible for discussing whether to terminate the study (Table 2). In this study, all expected AE records will also be used as safety indicators to evaluate the safety of e-SGB, which is mainly completed by the DMC and reported in the final trial publications. If e-SGB significantly increases the risk of certain adverse events or is related to an unexpected SAE that deteriorates the patient’s condition, such as aneurysm rupture and rebleeding before clipping, we will emphasize this in the final results.

If the patient’s health is damaged due to participation in this study, we will be responsible for taking appropriate treatment measures. The sponsor, Beijing Tiantan Hospital, Capital Medical University, will bear the treatment expenses and pay corresponding economic compensation to the patients according to relevant national regulations.

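### Table 2 has no criterion for lasting disability, so a permanent block-related nerve palsy that needs no intervention falls below the grade-3 serious threshold that a drained puncture hematoma meets

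*Protocol article*

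**What the plan says.** Table 2, in the section SGB-related complications, has five grades:

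- Grade 1 is for events that are only observed: "No need for drugs or surgery, endoscopy, or intervention"
- Grade 2 is for events managed with treatment that falls short of a procedure
- Grade 3 is for events that need a procedure: "Requiring surgical, endoscopic, or radiological intervention", split into 3a (no general anesthesia) and 3b (general anesthesia)
- Grade 4 is for threats to life: "Severe life-threatening complications need to be transferred to the intensive care unit or special care unit", split by whether one organ or several fail
- Grade 5 is death

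The same section calls complications of grade 3 or above serious. For these, extra follow-up may be needed, and in those cases the patient is unblinded. The section on adverse event monitoring uses the same cut-off to decide when the data monitoring committee (DMC) must consider ending the trial: "If there were any severe adverse events (SAEs) associated with the study (grading criteria ≥ 3), the DMC was responsible for discussing whether to terminate". Subarachnoid block is named as one example of a serious complication. No other general criterion for seriousness appears.

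The list of possible block complications opens with "Block or injury of nerve: recurrent laryngeal, phrenic, brachial plexus, and vagus nerves (30 min after e-SGB and during hospitalization" and closes with infection and hematoma at the puncture site.

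**The concern.** Safety is half of the stated objective, and block-related complications are declared safety indicators. The first item on the protocol's own list is nerve injury, with four nerves named. What matters most to a patient with such an injury is whether it lasts, and Table 2 has no place for that. An injury that cannot usefully be treated gets a low grade because nothing is done about it, while a brief, fully recovered event gets a high grade because a procedure was done.

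The grade-3 cut-off also drives action. It decides which events are called serious, which may bring extra follow-up and unblinding, and which the DMC must discuss with termination in view. If the scale misorders two harms that the protocol itself expects, the explicit action rule responds to the lesser one and not to the disabling one.

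**Working it through.** The article gives no figure to reproduce on this point, so the check is to apply Table 2 as a decision rule: assign the highest grade whose definition is met, then compare it with the cut-off of 3.

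**Inputs.** The grade definitions and the list of expected complications come from SGB-related complications. The cut-off comes from that section and from the adverse event section.

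**Rule.** Death gives 5; otherwise a life-threatening event needing intensive or special care gives 4; otherwise a procedure gives 3; otherwise any other treatment gives 2; otherwise 1. Serious means grade 3 or above.

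| Event | Definition met | Grade | Serious? |
|---|---|---|---|
| Permanent nerve palsy, observed only | no treatment | 1 | no |
| Permanent nerve palsy, drugs only | some treatment | 2 | no |
| Nerve palsy needing a surgical or endoscopic procedure | procedure | 3 | yes |
| Phrenic palsy, life-threatening, needing intensive care | life threat | 4 | yes |
| Puncture hematoma, observed only | no treatment | 1 | no |
| Puncture hematoma, drained without general anesthesia | procedure | 3a | yes |

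**Reading the table.**

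1. Rows 1 and 5 get the same grade, although one patient has a permanent deficit and the other has a hematoma that needed nothing done. How long the deficit lasts does not enter the grade.
2. Rows 1 and 6 are in the wrong order: the permanent deficit is below the threshold and the drained hematoma is above it.
3. Rows 3 and 4 show that a palsy can reach the threshold, but only through a procedure or a life threat, never because it persists.

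**What the label changes.** For rows 1 and 2 the event misses three things: the serious/SAE label, the possible additional follow-up with its unblinding, and the DMC discussion of termination. Other provisions of the adverse event section carry no grade limit. Study-related events are recorded and followed until they resolve or stabilize, events go to the ethics committee within 24 h, the DMC reviews all events reported there, and all expected events serve as safety indicators. The secondary outcome on complications up to 90 days has no grade limit either.

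**The case against.** The strongest reply is that oversight of low-grade events is intact. A permanent palsy is recorded, followed, reported, seen by the DMC and counted among complications, and global disability is measured by the mRS at discharge, 30 and 90 days. The scale is applied consistently in both sections, so nothing in the text contradicts it, and a treatment-based scale is a legitimate choice. Supplement Part 3, which holds the detailed definitions of the observed indicators, is not at hand.

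Most of this stands, and it limits the point to classification. It does not remove it. General review by the DMC is a different provision from the rule that says which events must prompt a discussion of termination, and that rule sorts these events wrongly. Table 2 and its cut-off are printed in full, so this is a stated rule and not a detail left to another document.

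A reader might infer more than the text supports:

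- *That the scale grades only by treatment, and a nerve palsy can never be serious.* Grade 4 rests on life threat and organ dysfunction and Grade 5 on death, and a palsy that needs a procedure or threatens life reaches Grade 3 or 4.
- *That Grade 4 is empty because* "All patients will be admitted to the ICU after the operation and then receive the standard of care". Routine admission is not a complication, and the life-threat wording and the organ-dysfunction split still discriminate.
- *That e-SGB safety is judged by a count of serious events, which would then be too low.* The article says no such thing; it uses all expected adverse event records.

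**Conclusion.** The point holds as a defect in the serious/SAE classification and its triggers, not in adverse event capture. A lasting block-related palsy that needs no procedure and is not life-threatening is Grade 1 or 2 and is not serious under the protocol. A puncture hematoma drained without general anesthesia is Grade 3a and is.

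This rests on two assumptions: that Table 2 is applied as written, and that drainage counts as a surgical intervention. No expected number of misclassified events can be given. The article states no rate for nerve injury and describes the incidence of block complications as low; with 1:1 allocation, 228 / 2 = 114 patients would be exposed to the block. The number of events is therefore likely to be small. The correction is worth making because it costs little and concerns the disabling form of a harm that the protocol lists first.

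**What to change.** Add one sentence under Table 2 and repeat it in the adverse event section: *an event that leaves persistent or significant disability at discharge or at day 90 counts as serious whatever its treatment grade.* Leave the five grades as they are.

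No new visit is needed. Table 1 already schedules complications at discharge and at day 30 or 90, and the Measurements section includes block-related complications among them. Because the listed observation time for nerve injury ends with the hospital stay, the sentence should say that the day-90 judgment uses the scheduled complication assessment.

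Keep the existing limits to block-related complications and to events associated with the study. Without them, disability from the hemorrhage itself would be swept in, and the Background puts the disability rate of the disease above one third.

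The cost is a few more events going to the DMC as serious, and possibly a few more unblindings where extra follow-up is needed. An event first classed as serious at day 90 cannot affect the primary outcome, which closes at 14 days after aSAH. For one classed at discharge, any blinded assessment due at that visit can be completed first.

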### Standardized anesthetic management

All recruited patients will receive unified perioperative anesthesia management (see Supplement Part 1 for details). Anesthesia with propofol, sufentanil, and remifentanil will be administered to maintain the target BIS values between 40 and 60. The fluctuations in SBP will be maintained within 20% of the baseline. For preoperative SBP > 160 mmHg, especially in patients with acute hypertension (SBP > 200 mmHg), SBP should be actively controlled to less than 160 mmHg regardless of the 20% range limit. During the perioperative period, it is necessary to maintain normal blood volume and avoid hypervolemia and hemodilution. Mechanical ventilation will avoid hypoxemia, hypercapnia, and hypocapnia. Since low hemoglobin may be detrimental to brain tissue oxygen supply, Hb > 10 g/dl or HCT > 30% should be maintained as much as possible. Blood glucose and electrolytes will be closely monitored and maintained in the normal ranges. Cerebral salt wasting syndrome will be treated with hydrocortisone or 3% saline. Finally, short-term prophylactic antiepileptic therapy is permitted in our center.

### Patient management after surgery

All patients will be admitted to the ICU and treated with a standard treatment protocol (see Supplement Part 2 for details) that includes intensive care monitoring, maintaining normotension (SBP 140 mmHg-220 mmHg) and normovolemia (positive fluid balance > 500 ml/day), decreasing intracranial pressure (ICP) and nimodipine therapy. Continuous intravenous infusion of nimodipine 0.8–2.0 mg/h is preferred at our center. Blood pressure will be maintained within a high threshold range in all patients, but we will not actively use induced hypertension to alleviate the ischemic symptoms. Likewise, hypervolemia and hemodilution will not apply in our center. Norepinephrine is the first choice as a vasopressor. Patients with severe cerebral edema or ICP greater than 20 mmHg will be treated with 3% NaCl saline or mannitol, preferably hypertonic saline, due to its minimal damage to the kidney. For patients with severe neurological deficits that cannot be explained by rebleeding, hydrocephalus, infection, surgical complications, etc., emergency DSA angiography will be performed, and intra-arterial vasodilators (Fasudil) or transluminal balloon angioplasty (TBA) will be given if necessary.

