### Patient population

#### Inclusion criteria

Patients with aSAH diagnosed by imaging (CTA or DSA) and scheduled for surgical intervention within the expected time period (48 h) will be assessed for recruitment. Those with an onset more than 48 h prior to assessment will not be included because CVS can occur on the third day after onset. The inclusion criteria were as follows: (i) 18 years ≤ age ≤ 65 years, (ii) planned aneurysm clipping, (iii) preoperative Hunt-Hess grade 1–3, and (iv) signed informed consent.

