### Measurements

The endpoint assessors, who are only responsible for postoperative follow-up, will regularly visit all patients at the planned time points (Table 1). The nurse will check the patients every 4 h. At 10:00 AM every day, the attending neurologist and nurse will evaluate whether the patient experienced symptomatic vasospasm in the last 24 h and record it in the case report form. All patients will receive brain imaging, including CT, CTA, and CTP examination, at least twice, before the operation and 5–8 days after the operation. Postoperative days 5–8 correspond to the peak period of CVS appearance 7–10 days after aSAH. Imaging aims to assess CTA vasospasm, cerebral perfusion, new hemorrhage (if present), and infarction. CT needs to be examined an additional two times, one within 24 h after the operation to assess whether new cerebral infarction or hemorrhage is caused by surgery and one at discharge to assess the occurrence of new cerebral infarction. The assessments will be completed mainly by an independent radiologist. All TCD monitoring will be performed by an experienced and specialized follower on the day before surgery (T0) and on the immediate (T1), 1st (T2), 2nd (T3), 3rd (T4), 5th (T5), 7th (T6), and 9th (T7) days after the operation. Delirium will be documented using the CAM-ICU during the first 3 days after the operation. Additionally, cognitive performance will be assessed at baseline and at 24 h, 7 days, 30 days, and 90 days after surgery using the Mini-Mental State Examination (MMSE). The modified Rankin scale (mRS) will be used to assess patient disability at discharge and at 90 days. The incidence of complications, including myocardial infarction, postoperative rebleeding, moderate and severe brain edema, pulmonary embolism, deep venous thrombosis, SGB-related complications, and unexpected adverse events, will also be recorded. All baseline and intraoperative data will be recorded by the resident anesthesiologists and the attending anesthesiologists who are responsible for recruitment and intervention.

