### Primary outcome

The primary efficacy outcome is the incidence of symptomatic vasospasm within 14 days after aSAH, which is defined as new focal or global neurological dysfunction or a decrease in the Glasgow coma score by more than two points, with angiographic vasospasm on TCD or CTA [34–36]. Symptoms must not be explainable by causes such as primary bleeding, rebleeding, hydrocephalus, fever, infection, electrolyte or metabolic disorders, and surgical complications.

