### Secondary outcomes

The secondary outcomes in the BLOCK-CVS trial include the following:Incidence of TCD vasospasm within 14 days after aSAH [34].Incidence of CTA vasospasm on days 5–8 after the operation [34].Incidence of abnormal perfusion monitored by CTP on days 5–8 after the operationIncidence of new cerebral infarction observed on days 5–8 after the operation and at dischargeContinuous cerebral blood flow velocity monitored by TCD on the day before surgery (T0) and on the immediate (T1), 1st (T2), 2nd (T3), 3rd (T4), 5th (T5), 7th (T6), and 9th (T7) days after the operationThe Mini-Mental State Examination (MMSE) score was assessed at 24 h, 7 days, 30 days, and 90 days after the operationIncidence of delirium as measured by CAM within 3 days after the operationTotal length of stay in the intensive care unit and hospitalModified Rankin Scale (mRS) score at discharge, 30 days, and 90 daysAll-cause mortality up to 90 daysIncidence of complications up to 90 days

See Supplement Part 3 for detailed definitions of all observed indicators.

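### Rescue for vasospasm can come before the only scheduled postoperative CTA/CTP, so a reopened vessel can be read as no CTA vasospasm and no perfusion deficit

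*Protocol article*

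**What the plan says.** Patient management after surgery describes rescue in both arms. The trigger is a severe deficit without another explanation: "For patients with severe neurological deficits that cannot be explained by rebleeding, hydrocephalus, infection, surgical complications, etc., emergency DSA angiography will be performed". The treatment that may follow this angiography is left to need: "intra-arterial vasodilators (Fasudil) or transluminal balloon angioplasty (TBA) will be given if necessary". The section sets no time limit and makes no link to the study scan.

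Measurements schedules CT, CTA and CTP "at least twice, before the operation and 5–8 days after the operation" and explains that "Postoperative days 5–8 correspond to the peak period of CVS appearance 7–10 days after aSAH". Table 1 marks CTA/CTP only before the operation and at days 7–10 from onset. Secondary outcomes then lists "Incidence of CTA vasospasm on days 5–8 after the operation" and gives abnormal perfusion on CTP the same window. It refers the reader onward: "See Supplement Part 3 for detailed definitions of all observed indicators". That supplement is not at hand.

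Inclusion criteria limits enrolment to 48 h from onset "because CVS can occur on the third day after onset". The primary outcome is symptomatic vasospasm within 14 days, "with angiographic vasospasm on TCD or CTA".

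The article does not say how a scan taken after rescue is classified. Rescue is not among the listed outcomes or the complications named under Measurements.

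**The concern.** Fasudil and angioplasty are given to dilate the vessel and restore flow. A patient treated on postoperative day 5 and scanned on day 7 may show an open artery and normal perfusion. Under an outcome defined by the finding on days 5–8, that patient, one of the most severe cases in the trial, becomes a non-event.

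Two secondary outcomes are at stake, together with the later TCD velocities (postoperative days 5, 7 and 9). The Discussion gives CTP the task of showing perfusion improvement after e-SGB and offers it as the answer to TCD false positives. A scan taken after rescue reflects the rescue as well as the block. A real effect on symptoms could then look less well supported by imaging than it is. Because rescue is not a reported outcome, readers could not tell from the listed outcomes whether this had happened.

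**Working it through.** **Order of events.** Vasospasm can begin on day 3 after onset (Inclusion criteria). The scan falls on days 7–10 after onset (Measurements, Table 1). That leaves 7 − 3 = 4 to 10 − 3 = 7 days in which spasm, deficit and rescue can all precede the scan. The missing-data rule in Statistical analysis (last observation, worst case) does not help, because a scan completed after rescue is not missing.

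**The plan's own figure.** Inputs from Sample size calculation: 45% vs 27%, 80% power, two-sided alpha 0.05, 5% loss. With unpooled variance,
n per arm = (1.960 + 0.842)² × (0.45×0.55 + 0.27×0.73) / 0.18² = 7.849 × 0.4446 / 0.0324 = 107.7, so 108.
108 / 0.95 = 113.7, so 114 per arm and 228 in total. This reproduces the plan, but it concerns the primary outcome. It serves here only to supply 108 evaluable patients per arm.

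**Effect on the imaging outcomes.** Let g be the share of symptomatic patients who are rescued before the scan and then read negative. Assume g is equal in both arms, and take the symptomatic rates as planned (45% and 27%). With true imaging rates P_C and P_T:
- observed control rate = P_C − 0.45g
- observed e-SGB rate = P_T − 0.27g
- observed difference = (P_C − P_T) − 0.18g

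The documents give neither g nor planned CTA/CTP rates, so the table is an illustration. It covers three assumed pairs of true rates. Power uses 108 per arm and a pooled-variance formula, which is why 45% vs 27% shows 79.1% and not 80%.

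| g | 45% vs 27%: difference, power | 50% vs 30%: difference, power | 70% vs 42%: difference, power |
|---|---|---|---|
| 0 | 18.0 points, 79.1% | 20.0 points, 85.6% | 28.0 points, 98.9% |
| 5% | 17.1 points, 75.8% | 19.1 points, 82.8% | 27.1 points, 98.3% |
| 10% | 16.2 points, 72.3% | 18.2 points, 79.8% | 26.2 points, 97.5% |
| 20% | 14.4 points, 64.9% | 16.4 points, 73.1% | 24.4 points, 95.3% |
| 30% | 12.6 points, 56.9% | 14.6 points, 65.7% | 22.6 points, 92.1% |

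The risk ratio is 0.60 in every cell, for example 21.6/36.0, 24.6/41.0 and 36.6/61.0 at g = 20%. With equal shares and proportional rates, only the absolute difference and the power fall.

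**Outcomes not tied to that scan.** The primary outcome rests on daily symptom review over 14 days, with confirmation by TCD or CTA at any point. TCD vasospasm within 14 days is built from serial readings, so lower velocities after rescue do not erase an earlier positive. One narrow route remains for the primary outcome. Its definition does not name DSA, and no TCD is scheduled on postoperative days 4, 6 or 8. A patient who goes straight to DSA and rescue between TCD visits may therefore have only post-treatment confirmation.

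**The case against.** The strongest reply is that the classification rule may exist. Detailed definitions sit in Supplement Part 3 and postoperative management in Supplement Part 2, neither of which is at hand. A reader might infer that rescued patients definitely are counted as event-free, but the article does not say so. It supports only that they can be, given the window it fixes for these outcomes and the absence of rescue from its outcome list.

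Several further points stand:
- Two scans are a minimum, so an earlier CTA at symptom onset is allowed. Rescue may also follow the scan, and it will not always normalise it.
- Only severe deficits qualify, which is a subset of symptomatic patients.
- CTA vasospasm includes asymptomatic spasm, and the Background cites radiographic rates up to 70%. The higher the true rate, the smaller the relative loss: at g = 10%, 1.8/28 = 6% with 70% vs 42%, against 1.8/18 = 10% with 45% vs 27%.
- A shift toward the null is conservative for a superiority claim.
- Reading the scan as observed, whatever treatment preceded it, is a legitimate treatment-policy approach. Replacing it with any rescue as an event would bring a discretionary treatment decision into a radiologist's reading.

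The last point is why the scan reading should stay as the main result. None of these points removes the gap: the article does not say how a reopened vessel is handled.

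**Conclusion.** The point holds as a limited one. Rescue can precede the only scheduled postoperative CTA/CTP, and under the outcomes as written a reopened vessel can be counted as no CTA vasospasm and no abnormal perfusion. If e-SGB works and rescue shares are similar in the two arms, each absolute difference shrinks by 0.18g: 0.9 points at g = 5%, 1.8 at 10%, 3.6 at 20%. The true size is unknown, since g has no source in the documents.

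Three stronger readings are tempting and not supported:
- **That about a third of the effect is lost.** This needs 40% of symptomatic controls but only 20% of symptomatic e-SGB patients to be rescued before the scan, with half reversed: 45% × 0.8 = 36.0% vs 27% × 0.9 = 24.3%, a difference of 11.7 points instead of 18. An effective block implies fewer symptomatic patients, not a lower rescue share among them.
- **That unblinded neurosurgeons make the direction unpredictable.** Randomization and blinding leaves neurosurgeons unblinded but blinds the postoperative treatment team. The documents do not say that neurosurgeons make the rescue decision.
- **That the primary outcome is undermined.** It largely escapes, as does 14-day TCD vasospasm.

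**What to change.** Keep the day 5–8 scan reading as the main result for CTA vasospasm and abnormal perfusion. After checking Supplement Part 3 for an existing rule, add the following:

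1. A prespecified analysis of both outcomes in which vasospasm seen on the emergency DSA and treated before the day 5–8 scan counts as an event, whatever the later scan shows.
2. A repeat of the TCD velocity comparison with values taken after rescue flagged and handled separately.
3. A report of rescue by arm through day 14: yes/no, date and type.

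This takes a short addition to the outcome definitions and the analysis section, plus one case report form item. The information should already be in the chart. There are two costs. The added analysis is broader than a pure scan reading, most of all for perfusion, where spasm on DSA stands in for a perfusion finding. And because recruitment is under way, changes to outcome indicators or statistical methods need ethics committee approval (Protocol amendment). The clinical criteria for giving rescue stay as they are.
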